### Design and setting

A prospective, multicenter, three-armed, permuted block-randomized, double-blind, placebo-controlled, prophylactic intervention study will be conducted in critically ill patients with a high risk of delirium development. All participating sites are members of the Dutch Intensive Care Unit Delirium Consortium facilitating the collaboration related to delirium research in the ICU. In all centers, patients are screened for delirium using the validated Dutch translation of the Confusion Assessment Method-Intensive Care Unit (CAM-ICU) [27-29] by well-trained ICU nurses, at least two times a day and more often if indicated (during periods of fluctuating symptoms or levels of sedation). Before initiation of the study, ICU nurses will receive additional information concerning the CAM-ICU on top of their in-house CAM-ICU training. Furthermore, during the study, inter-rater reliability measurements of the CAM-ICU and the Richmond Agitation Sedation Score (RASS), as part of the CAM-ICU, will be performed in order to check the quality of the assessments, and if necessary, additional training will be provided.

The study will start after training of all centers including an initiation visit.

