### Objectives

Definitions of variables in objectives are reported in Table 1.

**Table 1 T1:** Definition of study objectives

**Objective**	**Definition**
*Survival days in 28 days*	Number of days that patients survive in 28 days. All patients will be classified as either ‘alive at study day 28’ or, if dead, ‘dead at study day 28’ on an intention-to-treat basis.
*Delirium diagnosis*	Patients are diagnosed as delirious when they have at least one positive CAM-ICU screening during their complete ICU stay. Patients who were not delirious during their ICU-stay are considered as non-delirious patients.
*Delirium-and-coma-free days in 28 days*	Number of days that the patient is alive and not delirious and not in coma over 28 days starting from the day of inclusion. A delirium-and-coma-free day is defined as a negative CAM-ICU screening with a Richmond Agitation Sedation Score (RASS) greater than (more alert than) -3/-4/-5 during a day. In case a delirious patient is discharged to the ward, a delirium-free day is defined as a delirium observation scale score [30] of less than 3 during a complete day.
*Duration of mechanical ventilation*	Time in days that the patient is on the mechanical ventilator. If the patient is ventilated mechanically several times during one ICU admission, then the ventilator times are added. Both invasive and non-invasive ventilation will be registered. Ventilator-free days (in 28 days) will be calculated.
*Incidence of re-intubation*	Patients who need to be intubated within 28 days from randomization, following a previous extubation, irrespective of the reason for re-intubation, are counted as incident case for re-intubation.
*Incidence of ICU readmission*	Patients who need to be readmitted to the ICU during within 28 days from randomization, irrespective of the reason for readmission, are counted as incident cases for ICU readmission.
*Side effects*	Drowsiness, agitation, QTc-time prolongation (using 12-leads ECG or monitor strip with Bazett’s formula) and development of extra pyramidal symptoms such as tandem gait, dystonia, tremor, myoclonus, tics, rigidity, akathisia [31], determined daily by physical examination by the intensivist.
*Serious adverse event*	Any untoward medical occurrence or effect at any dose that results in one of the following outcomes and is not classified as a clinical outcome of delirium or the underlying disease using the description above:

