	- death that is not related to the underlying disease or sequel of the underlying disease, or death that is considered by the investigator to be related to study drug
	- prolonged inpatient hospitalization or re-hospitalization
	- a life-threatening experience (that is, immediate risk of dying)
	- persistent or significant disability/incapacity
	- congenital anomaly/birth defect
	- considered significant by the investigator for any other reason
*Sudden unexpected serious adverse reactions*	Unexpected adverse reactions are adverse reactions, of which the nature, or severity, is not consistent with the applicable product information. Adverse reactions are all untoward and unintended responses to an investigational product related to any dose administered.

#### **
*Primary objective*
**

To determine the effect of prophylactic haloperidol use on 28-days survival.

#### **
*Secondary objectives*
**

There are seven secondary objectives:

1. To determine the effect of prophylactic haloperidol use on 90-day survival; survival analysis stratifying for delirium incidence will be performed.

2. To determine the effect of prophylactic haloperidol use on the incidence of delirium.

3. To determine the effect of prophylactic haloperidol use on the number of delirium- and coma-free days in a period of 28 days.

4. To determine the effect of prophylactic haloperidol use on delirium related outcomes: time to successful extubation, incidence of re-intubation, incidence of ICU readmission, and incidence of unplanned removal of tubes and catheters.

5. To evaluate the incidence and severity of side effects of haloperidol prophylaxis.

6. To determine the effect of preventive haloperidol use on quality of life 1 and 6 months following ICU admission compared with a baseline measurement at ICU admission using the Short Form-12 (SF-12) questionnaire.

7. *A priori* defined post-hoc analyses:

a. To determine the preventive effectiveness of haloperidol in different patient groups based on the *a priori* risk to develop delirium: patients with a predicted risk up to 50%, 50–70%, 70–90%, above 90% will be evaluated.

a. To determine the preventive effectiveness of haloperidol in different patient groups: medical/surgical/trauma patients, per acute physiology and chronic health evaluation-II (APACHE-II) score (<20, 20–25, >25)

a. Effectiveness of prophylaxis when delirium is diagnosed based on 1, 2, or more days with positive CAM-ICU scoring.

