### End of study medication

Prophylactic treatment with haloperidol will be continued until day 28, or discharge from the ICU (whatever comes first), or until delirium occurs. In the latter case, patients will be subsequently treated according to the delirium treatment protocol (with higher dosage of open label haloperidol).

In case delirium occurs, the patient’s study medication (prophylaxis treatment) will be stopped and the patient will be treated with open label haloperidol according to the delirium treatment protocol described below. Analysis will be on intention-to-treat basis. Study medication will not be restarted once delirium subsides, therapeutic haloperidol is stopped, or when a patient is re-admitted to the ICU within 28 days.

#### **
*Delirium treatment*
**

Patients with delirium (defined as a positive CAM-ICU test) will be treated with 2 mg haloperidol intravenously three times daily. Patients suffering from *hypoactive* delirium (only RASS scores between 0 and -3) and patients aged ≥80 years, weighing ≤50 kg, or with liver failure, will be treated with a lower dosage of 3x1 mg intravenously. Dosage can be increased up to a maximum of 3x5 mg in case of serious agitation or anxiety due to delirium. Additionally, midazolam, clonidine, propofol, or dexmedetomidine can be used as an escape therapy in case of serious agitation with insufficient efficacy of haloperidol according to usual patient care.

In patients treated for more than three days, the dosage will be halved when delirium subsides. When delirium does not reoccur the following day (CAM-ICU remains negative), the dosage will be halved again and then stopped the third day when the patient remains non-delirious. In case delirium occurs again during the reducing phase, the original dose will be restarted.

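### Delirium-and-coma-free days run to day 28, but no ward assessment is stated for patients never delirious in the ICU, so ward ascertainment depends on an outcome the treatment is meant to change

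*Protocol article*

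**What the plan says.** The number of delirium- and coma-free days in 28 days is secondary objective 3 (Objectives) and is listed among the secondary endpoints in Table 2. Table 1 gives its window: "Number of days that the patient is alive and not delirious and not in coma over 28 days starting from the day of inclusion". The window is not limited to the ICU stay.

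Table 1 then gives two day rules:

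- **General rule:** "A delirium-and-coma-free day is defined as a negative CAM-ICU screening with a Richmond Agitation Sedation Score (RASS) greater than" the coma levels during a day. Design and setting says that the CAM-ICU is done "by well-trained ICU nurses, at least two times a day and more often if indicated". No CAM-ICU screening on the ward is described.
- **Ward rule:** "In case a delirious patient is discharged to the ward, a delirium-free day is defined as a delirium observation scale score" below 3 over a complete day. It is stated for a delirious patient and for nobody else, and it does not mention coma.

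Two other statements bear on the point. The delirium-diagnosis row of Table 1 reads "Patients are diagnosed as delirious when they have at least one positive CAM-ICU screening during their complete ICU stay", and it classes everyone else as non-delirious. End of study medication reads "Prophylactic treatment with haloperidol will be continued until day 28, or discharge from the ICU (whatever comes first), or until delirium occurs".

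**The concern.** For survivors, part of the 28-day window falls after ICU discharge. In that part, the article states an instrument only for patients who have been classed as delirious. Whether ward delirium can be found therefore depends on something that happens after randomisation and that prophylaxis is meant to reduce. Double-blinding does not remove this, because the selection works through the outcome and not through knowledge of the allocation.

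The timing of treatment adds to the problem. Study drug ends at ICU discharge. If haloperidol only held delirium back until then, the later episode would fall in a patient who counts as a prophylaxis success and for whom no ward score is foreseen. Delirium incidence cannot reveal this, since it is confined to the ICU stay. The free-day count is the one delirium endpoint whose window reaches past the ICU, and the Discussion expects the trial to support conclusions on preventing delirium. At stake is whether a difference on this secondary endpoint could be partly a difference in observation, or delay presented as prevention.

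**Working it through.** The plan gives no figure on this point to reproduce. The check is first a reading of the text, then an illustration of size.

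**Step 1: who is assessed on the ward.** The phrase about a delirious patient discharged to the ward has two possible meanings.

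| Patient group | If it means delirious at discharge | If it means ever CAM-ICU positive in the ICU |
|---|---|---|
| Delirious at ICU discharge | ward scale | ward scale |
| ICU delirium, resolved before discharge | none stated | ward scale |
| Never delirious in the ICU | none stated | none stated |

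The second meaning matches the diagnosis row of Table 1, and the text does not settle the choice. The last row is the same under both meanings, so the point does not depend on it.

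**Step 2: how the unassessed days are scored.** The endpoint opens as days alive, not delirious and not in coma, and Table 1 classes patients without ICU delirium as non-delirious. Read together, their ward days count as free without assessment.

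**Step 3: size if ward delirium is unrelated to prophylaxis.** Let p be the proportion with ICU delirium, w the probability of ward delirium in a patient never delirious in the ICU, and d its duration in days. Assume that w and d are equal in the two arms and that ward delirium in ICU-delirious patients is fully recorded.

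- Unseen delirious days per patient: U = (1 − p) × w × d
- Spurious gain for haloperidol: B = U(haloperidol) − U(placebo) = [p(placebo) − p(haloperidol)] × w × d

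Inputs from the Background: a median predicted risk of about 35%, and incidences of 75% (control) and 65% (prophylaxis) in the earlier high-risk study. Assumed inputs: haloperidol-arm rates of 30% and 25% against 35%, w from 10% to 30%, and d from 2 to 3 days.

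| ICU delirium, placebo vs haloperidol | w, d | U placebo | U haloperidol | B |
|---|---|---|---|---|
| 35% vs 30% | 10%, 2 | 0.65 × 0.1 × 2 = 0.130 | 0.70 × 0.1 × 2 = 0.140 | 0.010 |
| 35% vs 30% | 30%, 3 | 0.65 × 0.3 × 3 = 0.585 | 0.70 × 0.3 × 3 = 0.630 | 0.045 |
| 35% vs 25% | 10%, 2 | 0.130 | 0.75 × 0.1 × 2 = 0.150 | 0.020 |
| 35% vs 25% | 30%, 3 | 0.585 | 0.75 × 0.3 × 3 = 0.675 | 0.090 |
| 75% vs 65% | 10%, 2 | 0.25 × 0.1 × 2 = 0.050 | 0.35 × 0.1 × 2 = 0.070 | 0.020 |
| 75% vs 65% | 30%, 3 | 0.25 × 0.3 × 3 = 0.225 | 0.35 × 0.3 × 3 = 0.315 | 0.090 |

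The range is 0.01 to 0.09 day per patient.

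**Step 4: size if prophylaxis only postpones.** Assume that 15% of placebo and 10% of haloperidol patients carry delirium to the ward, that each such patient has 3 ward delirium days, and that the missing 5% on haloperidol become delirious on the ward instead, also for 3 days.

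- Placebo, recorded: 0.15 × 3 = 0.45 day
- Haloperidol, recorded: 0.10 × 3 = 0.30 day; unrecorded: 0.05 × 3 = 0.15 day
- True difference: 0.45 − (0.30 + 0.15) = 0
- Recorded difference: 0.45 − 0.30 = 0.15 day in favour of haloperidol

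On the 28-day scale, 0.09 / 28 is about 0.3% and 0.15 / 28 about 0.5%.

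**Step 5: the ICU day rule.** At least two screenings are made per day, and the general rule speaks of a negative screening during a day, whereas the ward rule speaks of a complete day. The article does not say how an ICU day with one positive and one negative screening is scored.

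**The case against.** The strongest reply is that the article never says other patients go unassessed. It is silent on them, it condenses a fuller protocol that is not shown, and ward procedures for them may be described there. That is fair as to what sites may actually do. It does not remove the point: the article does fix a ward rule, and it makes that rule conditional on delirium. Followed as written, the rule gives an uneven comparison.

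Several stronger readings are tempting, and the text does not support them:

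- **That patients with resolved ICU delirium certainly have no ward score.** Table 1's own definition of a delirious patient may cover them.
- **That a patient discharged well on day 5 can score at most 5 of 28, for want of a negative CAM-ICU on the ward.** The opening of the definition and the classing of such patients as non-delirious point the other way.
- **That most of the window is unassessed.** With an assumed ICU stay of 3 to 7 days, 25 to 21 of the 28 days (89% to 75%) follow the ICU. That share includes days after hospital discharge, which would reasonably count as free in any case.
- **That one negative screening makes a day free despite a positive one.** The definition also requires the patient to be not delirious. The wording needs clarifying, but it does not say this.

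It is also fair that the rule is the same in all arms, that every rate in the illustration is assumed, and that a material effect is not shown.

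**Conclusion.** The point holds for one secondary endpoint. Under either meaning of the ward rule, patients never delirious in the ICU have no stated ward assessment and are in effect credited with free days, so ascertainment depends on an outcome the treatment is meant to change.

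The bias runs towards the arm with less ICU delirium, which is haloperidol if prophylaxis works in the ICU. It is probably small: 0.01 to 0.09 day per patient if ward delirium is unrelated to prophylaxis, and 0.15 day if a 5-point difference is entirely postponement. It would be larger if ward delirium were more common or longer than assumed. The direction and the dependence on the outcome follow from the text; the sizes rest on assumed rates.

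A reader might infer that the trial's main conclusion or its delirium incidence is compromised. Neither is. The primary endpoint, 28-day survival, does not use these assessments, and incidence is explicitly limited to the ICU stay.

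**What to change.** Keep the 28-day window and apply one post-ICU rule to every patient, whatever their ICU delirium status:

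1. Where delirium observation scale scores are available for all patients still in hospital, use them for all.
2. Otherwise, count post-ICU days alive as free in all patients for the between-arm comparison. Report the version with the selective ward scores as a sensitivity analysis, and limit the conclusion to delirium in the ICU. This default makes the ward rule even, but it cannot show postponed delirium, hence the narrower claim.
3. State that an ICU day counts as free only if all CAM-ICU screenings that day are negative and the RASS is above the coma threshold.
4. Say whether a delirious patient in the ward rule means delirious at discharge or ever CAM-ICU positive, so that the sensitivity analysis is reproducible.

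Do not replace the endpoint with a count of ICU days only. Such a count depends on ICU length of stay: a patient discharged well on day 3 could score at most 3, while one who stayed 20 days could score far more, so an arm with shorter stays would be penalised.

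The cost is a few lines in Table 1 and the analysis text and slightly more analysis work. If the default rule is used, ward delirium information is lost from the main comparison and the claim is narrower.

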### Study population

#### **
*Inclusion criteria*
**

All consecutive critically ill patients admitted to the ICU aged ≥18 years at the time of ICU admission and with an expected length of ICU stay of over one day will be included as informed consent is obtained.

Data from patients that are included in the study, but who do not receive any study drug and are discharged from the ICU within 24 h will be discarded from further analysis. Patients who received at least one dose will remain in the study and patients in whom study medication had to be halved or stopped, e.g., because of prolonged QTc time or other side effects, will remain allocated to their study group and analyzed on an intention-to-treat basis.

#### **
*Exclusion criteria*
**

The following will be considered exclusion criteria: no informed consent obtained; history of epilepsy, Parkinson’s disease, hypokinetic rigid syndrome, dementia or alcohol withdrawal syndrome; patients admitted to the ICU for any other neurological disease (including post-cardio-pulmonary resuscitation patients, and patients admitted with coma due to overdose); patients treated with anti-psychotic therapy over the last 30 days prior to ICU admission; prolonged QTc-time (>500 msec) or history of clinically relevant ventricular arrhythmia in last 12 months; pregnancy/breast feeding; documented delirium prior to ICU admission; reasons that impair delirium assessment with the CAM-ICU (serious auditory or visual disorders, unable to understand Dutch or English; severely mentally disabled; serious receptive aphasia); ICU-stay less than one day; moribund and not expected to survive two days; known allergy to haloperidol.

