### Intervention and control group

This study involves a comparison of prophylactic haloperidol in a dosage of 1 mg (intervention group 1) or 2 mg (intervention group 2) administered as a bolus intravenously three times a day compared with placebo of 0.9% sodium chloride (control group) administered intravenously three times a day in a double-blind fashion. All ampoules and drug boxes have an identical appearance.

To decrease the likelihood of encountering side effects in specific cohorts, the dose of the study drug will be halved in patients aged ≥80 years, weighing ≤50 kg, suffering from liver failure (indicated by serum bilirubin level >50 μmol/L) present at time of inclusion or during the study. Patients with an adjusted dose remain allocated to their original group (intention-to-treat).

Patients with an adjusted dose remain allocated to their original group (intention to treat).

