### Safety monitoring and safety issues

A Data Safety Monitor Board (DSMB) is established for this study to perform ongoing safety surveillance and to perform interim analyses on the safety data. This is an independent committee composed of two physicians/researchers (a psychiatrist and an anesthetist) and a statistician. The DSMB will perform all interim analyses. To assess side effects of haloperidol and to determine superiority of the intervention or placebo the DSMB will be unblinded for this study, while all researchers remain blinded. Furthermore, the study will be monitored by an independent researcher who will monitor the trial master file, and perform random checks of informed consent forms, drug accountability lists, and source data of primary and secondary outcome measures.

Concerning safety issues, during a patient’s treatment with the study medication, known side effects of haloperidol [34] are pro-actively collected with a special focus on prolonged QTc-time, drowsiness, extrapyramidal symptoms, and agitation and sedation effects. All side effects will be collected during patients’ treatment with the study medication until 24 h after stopping the study medication. In case of the occurrence of side effects, physicians can reduce the dosage or stop the study medication, depending on the severity of the occurred side effect and at the discretion of the attending physician. Only for prolonged QTc-time, strict stopping rules are applied, as described below. To detect side effects of haloperidol, the protocol dictates that patients are physically examined every day for known signs of extrapyramidal symptoms (signs of Parkinsonism and/or akathisia and/or dystonia). Furthermore, daily QTc-time is calculated using a 12-lead ECG or a monitor lead ECG. A QTc-time of over 500 msec combined with an increase of over 10% of baseline QTc-time is defined as prolonged QTc-time. In case of QTc-time prolongation, the study drug is temporarily stopped until QTc-time is normalized. After normalization of QTc-time (<500 msec) the study drug will be restarted. If QTc-time becomes prolonged again, the study drug will be stopped definitively. The patient will remain allocated to the original study group.

To determine long-term side effects, such as rigidity, and quality of life, a recommended and validated quality of life questionnaire, SF-12 [35], is taken at the time of admission and is sent to the patients 1 and 6 months after ICU admission.

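### The QTc side-effect outcome rests on Bazett's formula alone, so changes in heart rate can create or hide cases of prolongation; an analysis with a second correction would help interpret it.

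*Protocol article*

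**What the plan says.** All references are to the protocol article.

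- **Formula.** The side-effects row of Table 1 (Objectives) lists QTc prolongation as measured "using 12-leads ECG or monitor strip with Bazett’s formula". No other correction appears in the article.
- **Definition of a case.** Safety monitoring and safety issues: "A QTc-time of over 500 msec combined with an increase of over 10% of baseline QTc-time is defined as prolonged QTc-time". Both conditions must hold together.
- **Frequency.** The same section: "daily QTc-time is calculated using a 12-lead ECG or a monitor lead ECG". The formula is not repeated there.
- **Consequence.** "In case of QTc-time prolongation, the study drug is temporarily stopped until QTc-time is normalized". A second prolongation ends study drug for good.
- **Entry limit.** Study population excludes "prolonged QTc-time (>500 msec) or history of clinically relevant ventricular arrhythmia in last 12 months", so a baseline QTc of up to 500 msec is eligible.
- **Role.** The outcome belongs to the fifth secondary objective: "To evaluate the incidence and severity of side effects of haloperidol prophylaxis".
- **Comparator.** Placebo is "administered intravenously three times a day in a double-blind fashion" (Intervention and control group).

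**The concern.** Bazett's formula divides QT by the square root of the RR interval. If QT in fact varies with RR less steeply than a square root, the formula over-corrects: QTc goes up when the heart speeds up and down when it slows, with no change in repolarisation. The safety section compares each daily value with a fixed limit and with the patient's own baseline. Any change in heart rate between baseline and the day of measurement therefore enters the outcome.

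QTc prolongation is the only ECG measure among the side effects in Table 1, and the only side effect with a strict stopping rule. If part of the case count reflects heart rate, the haloperidol-placebo difference on this outcome is harder to read. A null result would be less reassuring than it looks.

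**Working it through.** The plan states no figure on this point, so there is nothing to reproduce. The check asks how far heart rate alone moves Bazett QTc, and then applies the full two-part definition.

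**Inputs from the article:** Bazett's formula (Table 1); over 500 msec combined with over 10% above baseline (safety section); baseline up to 500 msec (exclusion criteria).

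**Assumption, not in the article:** without a drug effect, uncorrected QT is proportional to RR^b. The value of b is unknown, so a range is shown. The heart rates are illustrations.

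**Step 1, shift from rate alone.** Bazett QTc = QT/RR^0.5, and RR is inversely proportional to heart rate (HR), so

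QTc after / QTc before = (HR1/HR0)^(0.5 − b).

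For 80 to 110/min the ratio is 110/80 = 1.375:

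| b | 80 to 110/min | 110 to 80/min |
|---|---|---|
| 0 | 1.375^0.5: +17.3% | −14.7% |
| 0.25 | 1.375^0.25: +8.3% | −7.7% |
| 1/3 | 1.375^(1/6): +5.5% | −5.2% |
| 0.5 | 0% | 0% |

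**Step 2, rate ratio that gives +10%.** This is 1.10^(1/(0.5 − b)): 1.21 at b=0, 1.46 at b=0.25, 1.77 at b=1/3, 2.59 at b=0.4, and never at b=0.5.

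**Step 3, the full definition.** QTc must rise by the larger of 10% and 500/baseline. The two are equal at 500/1.10 = 454.5 msec. Below that baseline the 500 msec limit is the harder condition; above it, the 10% rise is. Rate ratio needed if nothing but heart rate changes:

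| Baseline QTc | QTc ratio needed | b=0 | b=0.25 | b=1/3 |
|---|---|---|---|---|
| 400 msec | 1.25 | 1.56 | 2.44 | 3.81 |
| 440 msec | 1.136 | 1.29 | 1.67 | 2.15 |
| 455–500 msec | 1.10 | 1.21 | 1.46 | 1.77 |

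**Step 4, smaller rate shifts plus a modest true change (b=1/3, baseline 460 msec).** A true change here means the change at constant heart rate.

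- *Created case.* True +5% gives 460 × 1.05 = 483 msec, which is not a case. With 80 to 110/min the reading is 1.05 × 1.0545 = 1.107, or +10.7%. That is 509 msec, a case.
- *Hidden case.* True +12% gives 460 × 1.12 = 515 msec, a case. With 110 to 80/min the reading is 1.12/1.0545 = 1.062, or +6.2%. That is 489 msec, not a case.

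**Step 5, the absolute limit.** Fridericia's correction uses RR^(1/3), so Fridericia QTc = Bazett QTc × RR^(1/6), with RR in seconds. A Bazett value of 500 msec equals 500 × 0.6^(1/6) = 459 msec at 100/min and 500 × 0.5^(1/6) = 445 msec at 120/min.

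**The case against.** **The definition has two parts.** A reader might infer that a faster heart rate alone, by lifting QTc 10%, makes a patient count as prolonged. The article does not support that: the 10% rise counts only together with a value over 500 msec. From 60 to 110/min at b=1/3 the shift is (110/60)^(1/6) = 1.106, yet a baseline of 440 msec reaches only 487 msec. This objection stands, and it confines the pure-rate case to high baselines and large rate rises.

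**No arm-specific mechanism is documented.** A reader might also infer that haloperidol calms patients, slows the heart and so masks its own QT effect. The article reports no effect of haloperidol on heart rate, and it lists both drowsiness and agitation as possible side effects, so not even the direction is given. Study drug also stops when delirium occurs (End of study medication), and side effects are collected only until 24 h after stopping. Most delirious time therefore falls outside the window. This stands too: in a blinded, placebo-controlled trial, rate shifts unrelated to treatment do not favour an arm.

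**The exponent is assumed.** At b=0.5 Bazett is exact and the concern disappears. This is why a range is shown.

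**It is detail for another document.** A condensed article may leave case-report fields and extra tables to the full protocol or the analysis plan, and heart rate must be read anyway to compute Bazett. So the absence of a statement that heart rate is stored is no fault. But the article does fix the formula; the point concerns a stated method, not a gap.

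**The role is modest.** QTc is one of several side effects within one of seven secondary objectives, and the monitoring board's safety analyses use serious adverse events. This stands and limits the weight of the point.

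**Conclusion.** The concern holds in a limited form. For any b below 0.5, a Bazett-only QTc outcome depends partly on heart rate: by 5.5% at b=1/3 and 8.3% at b=0.25 for a change from 80 to 110/min. Rate alone meets the full definition only with a high baseline and a large rise. Smaller shifts matter where a patient is already near the limits, and they misclassify in both directions.

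The expected result is misclassification that is similar in all arms and dilutes the haloperidol-placebo contrast on this outcome. The amount of dilution cannot be computed, because the article gives no heart rates, no QTc distribution and no value of b. Bias between arms would need an effect of the drug on heart rate, which the article does not state.

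This is a weakness in the choice of a safety measure. It is neither a contradiction nor a wrong figure, and the primary endpoint, sample size and alpha are untouched.

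**What to change.** Keep the QT interval and the heart rate (already needed for Bazett) with each daily QTc value and with the baseline value. Analyse the QTc side-effect outcome with Fridericia's correction, or with heart rate as a covariate, and report the Bazett result alongside.

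Fridericia is exact only at b=1/3. For 80 to 110/min it leaves 1.375^(1/3 − 0.25) = 1.027, or +2.7%, at b=0.25, and 1.375^(1/3 − 0.5) = 0.948, or −5.2%, at b=0.5. The covariate analysis does not fix b in advance. Agreement between the analyses would show that the result does not hinge on the correction.

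The cost is small: two numbers kept per daily recording and one extra table. The downside is that the report carries two QTc definitions, with case counts that will differ, so which one leads should be fixed before unblinding. The change concerns the analysis only; the bedside stopping rule is not addressed here.
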